**Exclusion criteria**
Failure to meet the inclusion criteriaSimultaneous participation in other studiesLack of written informed consentHistory of a myocardial infarction or stroke within the past 6 monthsPainful arthritis, spinal stenosis, amputation, painful foot lesions, or neuropathy, limiting balance and mobilityUncontrolled hypertensionAdvanced Parkinson disease or other neuromuscular disorderDiagnosis of metastatic cancer or treatment with immunosuppressive therapySignificant visual or hearing impairment

Following the medical visit, the investigator will contact the potential participant by email or telephone to discuss the study and confirm their interest in participation. At this stage, detailed information about the study procedures will be provided, and written informed consent will be obtained before any study-related activities are initiated. The schedule for the visits and the procedures for conducting the research at the participant’s home will then be agreed upon according to participant availability. When recruitment is complete, participants included in the study will undergo all routine clinical investigations, such as collection of blood samples to assess their glycemic and lipid profiles and measurement of BMI. In addition, a researcher will perform the preliminary evaluation (T0). The scales described in Textbox 2 will be administered, and then an interview will be conducted. The participant will undergo training sessions at the study centers with the other study participants. After 10 weeks, the final evaluation will be conducted (T1). Participants will be required to complete a series of questionnaires, the details of which can be found in Table 1. During this phase, blood sample collection and BMI measurement will not be performed.

During the 2 follow-up visits (1 month and 6 months following the conclusion of the intervention), any alterations in the patient’s medical history will be recorded. All routine clinical investigations and all planned assessment scales will be administered. Blood sample collection to assess the glycemic and lipid profiles and BMI measurement will be performed exclusively at T3.

Textbox 2.Outcomes of the study.

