**Secondary outcomes**
Improvement in self-efficacy, evaluated using the Diabetes Management Self-Efficacy Scale (DMSES) [20]Reduction in emotional distress related to diabetes, measured using the Problem Areas in Diabetes Questionnaire (PAID) [21]Improvement in psychological well-being, assessed using the Psychological Well-Being Scale (PWB) [22]Improvement in quality of life (QoL), assessed using the EQ-5D-5L Visual Analog Scale (VAS) [23] and 12-item Short Form Health Survey (SF-12) [24]Reduction in body weight (measure routinely collected at the Diabetology Unit)Reduction in BMI (measure routinely collected at the Diabetology Unit)Improvement in the glycemic profile (glycated hemoglobin; measure routinely collected at the Diabetology Unit)Improvement in the lipid profile (directly related to cardiovascular risk; measure routinely collected at the Diabetology Unit)Collection of information about the participants’ experience with the training, their level of satisfaction, any benefits they have experienced, and any improvement suggestions, using an ad hoc questionnaireImprovement in health literacy, assessed using the 16-item European Health Literacy Survey Questionnaire (HLS-EU-Q16) [25]

**Table 1. T1:** Tools and dimensions of the protocol.

Dimension	Tool	R^a^	T0^b^	T1^c^	T2^d^	T3^e^
Cognitive status	MMSE^f^	X	—^g^	—	—	—
Psychological status	GDS^h^ 5-item version	X	—	—	—	—
General information	Sociodemographic questionnaire	X	—	—	—	—
Quality of life	EQ-5D-5L VAS^i^, SF-12^j^	—	X	X	X	X
Psychological well-being	PWB^k^ (18 items)	—	X	X	X	X
eHealth literacy	eHEALS^l^	X	—	X	X	X
Health literacy	HLS-EU-Q16^m^	—	X	X	X	X
Diabetes-related emotional distress	PAID^n^	—	X	X	X	X
Self-efficacy	DMSES^o^	—	X	X	X	X
Training experience	Ad hoc questionnaire	—	—	—	—	X

a R: recruitment.

b T0: first evaluation.

c T1: final evaluation.

d T2: follow-up 1 month after the end of the training.

e T3: follow-up 3 months after the end of the training.

f MMSE: Mini-Mental State Examination.

g not applicable

h GDS: Geriatric Depression Scale.

i VAS: Visual Analog Scale.

j SF-12: 12-item Short Form Health Survey.

k PWB: Psychological Well-Being Scale.

l eHEALS: eHealth Literacy Scale.

m HLS-EU-Q16: 16-item European Health Literacy Survey Questionnaire.

n PAID: Problem Areas in Diabetes Questionnaire.

o DMSES: Diabetes Management Self-Efficacy Scale.

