Module V is designed to encourage participants to self-reflect, with the objective of evaluating their level of awareness, knowledge, and skills in technology and digital health literacy. This session represents the final stage of the training program, including a component dedicated to evaluating the effectiveness of the educational activities and methods used during the program. The method adopted involves a trainer guiding participants through the completion of the final questionnaire, explaining its characteristics and providing practical support during the completion. During this phase, participants will complete a series of validated instruments, described in detail in the Results section of the protocol, which will measure changes in quality of life, psychological well-being, health literacy, eHealth literacy, self-efficacy, and diabetes-related distress. The use of standardized scales ensures that the assessment is measurable and comparable across multiple time points, thereby providing clear indicators of the program’s effectiveness. This quantitative evaluation is complemented by a final discussion, in which participants’ reflections, feedback, and suggestions for maintaining the skills acquired will be collected. Consequently, the evaluation process evolves from a mere descriptive exercise to one that is also actionable, as the collected data will be systematically analyzed and used to identify strengths and areas for improvement, guiding the refinement of future training cycles. The module includes instructions for completing the questionnaire, reflecting on personal progress in relation to the training objectives, and receiving constructive feedback. By actively participating in this self-assessment process, participants will have the opportunity to strengthen their digital and health literacy skills, while trainers will use the information gathered to optimize future training initiatives and ensure continuous improvement of digital health literacy interventions. In this manner, the program combines theory and practical application to foster ongoing change and hold participants accountable for their learning journey.

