### Outcomes

The primary end point of the study is defined as an improvement in eHealth literacy following the implementation of the training program, scheduled to span a period of 10 weeks, as described in Textbox 2. Then, the field trials will focus on improvements in health literacy, self-efficacy, psychological well-being, and quality of life, in addition to glycemic and lipid profiles. Moreover, the study aims to minimize emotional distress and reduce body weight and BMI, as shown in Textbox 2.

For these reasons, the protocol includes study-specific questions on demographics, emotional distress, psychological well-being, and physiological aspects. All scales used in the study have been validated in the languages of the pilot sites and are deemed suitable for administration to the patients enrolled in the study. Data will be collected at baseline (T0), immediately post intervention (T1), and at the 1-month (T2) and 6-month (T3) follow-up visits, as detailed in Table 1.

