### Statistical Analysis

The eHEALS score was used for sample size calculation. Specifically, the sample size was determined using the combination of a pilot study [26] and a larger study [27].

In the first case, considering a 1-tailed *t* test for paired samples in which the primary outcome eHEALS score varies from a mean of 24.3 (SD 8.9) to 28.4 (SD 8.1) [26], corresponding to an effect size of 0.48, an α error of .05 and a power of 90%, the sample size should be 39 participants. Considering a dropout rate of 15%, the sample size increases to 45 participants. While larger effect sizes reported in the literature [27] would suggest even smaller sample sizes, we decided to include 200 participants for several reasons: (1) to ensure robust and generalizable results across a diverse population of older adults with type 2 diabetes, (2) to account for potential variability in baseline eHealth literacy and other characteristics, (3) to maintain statistical power for secondary outcomes and subgroup analyses, and (4) to address existing gaps in the literature by providing sufficiently powered evidence on the efficacy of the intervention.

The initial phase of the data analysis will entail the description of the sample. Continuous variables will be reported as either the mean and SD or the median and IQR on the basis of their distribution (assessed using Kolmogorov-Smirnov test). Categorical variables will be expressed as an absolute number and percentage. In the context of group comparisons, continuous variables will be compared using independent or 2-tailed paired *t* tests for normally distributed data and Mann-Whitney *U* or Wilcoxon signed-rank tests for nonnormally distributed data, whereas categorical variables will be compared using chi-square or Fisher exact tests, as appropriate. A significance level of *P*<.05 will be applied. Corrections for multiple comparisons (eg, the Bonferroni or Holm method) will be applied where necessary. The results will be compared with the data from the other partner countries. Descriptive statistical analyses will be performed on the quantitative data with SPSS software (version 29.0.1.0; IBM Corp) or Rstudio (version 4.4.1; Posit PBC).

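### The training-experience questionnaire is scheduled at T3 only, which exposes a listed secondary outcome to delayed recall and to selection by who is still in the study

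*Protocol article*

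**What the plan says.** - **Status of the outcome.** Textbox 2 includes among the secondary outcomes: "Collection of information about the participants’ experience with the training, their level of satisfaction, any benefits they have experienced, and any improvement suggestions". The tool is an ad hoc questionnaire. No direction, hypothesis or test is attached. The Abstract says these findings are to guide how the programme is scaled up and improved.
- **Schedule.** In Table 1 the Training experience row ("Ad hoc questionnaire") is empty at recruitment, T0, T1 and T2 and marked only at T3.
- **When T3 falls.** The Table 1 footnote reads "T3: follow-up 3 months after the end of the training". The Outcomes section puts data collection "at the 1-month (T2) and 6-month (T3) follow-up visits, as detailed in Table 1". The text after the exclusion criteria agrees with the latter: "During the 2 follow-up visits (1 month and 6 months following the conclusion of the intervention". The Abstract and the Field Trial section also give 6 months.
- **End of training.** Module V, the last session, is described as "including a component dedicated to evaluating the effectiveness of the educational activities and methods used during the program". There, "participants will complete a series of validated instruments, described in detail in the Results section of the protocol". The constructs listed are quality of life, well-being, health and eHealth literacy, self-efficacy and distress. A trainer guides completion, and a final discussion collects reflections and suggestions. The ad hoc questionnaire is not mentioned.
- **Attrition.** The only figure is in Statistical Analysis, in the sentence that begins "Considering a dropout rate of 15" (per cent).

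**The concern.** A questionnaire about a course is most informative when the course is fresh and when people who did not finish can also answer. With a single administration at T3, neither condition is met.

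Participants judge five sessions from a distance of months. Anyone lost before T3 contributes nothing, including anyone who left because the training was too hard, inconvenient or unhelpful. The document recognises that such losses are possible: Participant Recruitment says the eligibility criteria are partly meant to limit attrition from difficulty with sessions or questionnaires, and the Discussion names digital access and digital literacy as barriers. The views of these people bear most directly on refinement.

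At stake is a descriptive result that could look more favourable than the experience of everyone who started, plus session-level feedback that is poorly remembered. Answers not collected at T1 or at withdrawal cannot be recovered afterwards.

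**Working it through.** **1. Recall interval.** Intervention Through Training has 5 modules, one every other week, so Module I precedes Module V by 4 × 2 = 8 weeks, about 2 months. At T3, Module I is recalled after about 3 + 2 = 5 months (footnote) or 6 + 2 = 8 months (other sections). The Abstract instead describes weekly sessions, which makes the gap 4 × 1 = 4 weeks and the intervals about 4 or 7 months. The delay is months on every reading.

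**2. Module V against Table 1.** The constructs listed for Module V are those Table 1 marks at T1. Module V refers to the Results section for its instruments, and Results refers back to Table 1, where Training experience is empty at T1. The passages are consistent: validated scales and a discussion at the end of training, the ad hoc questionnaire later. What is unstated is how the discussion relates to the listed outcome.

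**3. What the 15% measures.** The plan gives no figure for this outcome. Its 15% belongs to the eHEALS sample size. That calculation reproduces: a one-sided paired t test with effect size 0.48, alpha .05 and power 90% needs 39, and 39 × 1.15 = 44.85, rounded up to 45. (Dividing by 0.85 gives 46, which is immaterial beside the planned 200.) The Abstract defines the primary outcome as change from baseline to post intervention, so the natural reading of the 15% is loss by T1. No figure is given for loss between T1 and T3.

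**4. Illustration of selection.** Let s be the share satisfied among T3 responders and d the fraction of enrolled participants lost by T3. Satisfaction among the lost can be anything from 0% to 100%, so for all enrolled:

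- lower bound = s(1 − d)
- upper bound = s(1 − d) + d
- largest overstatement = s·d; largest understatement = (1 − s)·d

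All values of s are assumptions. So are all values of d, including 15% when it is carried through to T3. With s = 0.90, d = 0.15 and N = 200: 200 × 0.85 = 170 respond and 0.90 × 170 = 153 are satisfied. The bounds are 153/200 = 76.5% and (153 + 30)/200 = 91.5%.

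| Assumed s | Assumed d | Range for all enrolled | Overstated by at most | Understated by at most |
|---|---|---|---|---|
| 90% | 15% | 76.5% to 91.5% | 13.5 points | 1.5 points |
| 90% | 25% | 67.5% to 92.5% | 22.5 points | 2.5 points |
| 80% | 5% | 76% to 81% | 4 points | 1 point |
| 80% | 15% | 68% to 83% | 12 points | 3 points |
| 80% | 30% | 56% to 86% | 24 points | 6 points |

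The asymmetry follows from assuming that most responders are satisfied. It is not evidence on who drops out: if lost and retained participants are equally satisfied, the bias is zero.

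**5. What adding T1 recovers.** Split d into d1 (lost by T1) and d2 (lost between T1 and T3). A T1 questionnaire reaches the d2 group but not the d1 group. If the whole 15% is lost by T1, adding T1 recovers nobody. If all of it is lost afterwards, T1 recovers everybody. Only a form offered when someone stops attending reaches the d1 group.

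**The case against.** **T3 is a defensible time.** The outcome includes benefits experienced, and the programme aims at lasting behaviour change, so both need time to judge. In Module V a trainer guides completion, so satisfaction asked in that setting invites polite answers. This stands: it is a reason to keep T3 and to separate a T1 form from the trainer, but not to rely on T3 alone.

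**Feedback is already gathered at the end of training.** The Module V discussion is explicitly meant to improve later cycles, so the refinement purpose is partly served. This also stands. The discussion does not use the tool named for the secondary outcome, however, and it misses those who left before the last session.

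**Little depends on the item.** It is descriptive, and the article is condensed; the full protocol may provide for feedback from people who withdraw. That limits the severity. The T3-only marking, by contrast, is fixed in the article.

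**Stronger readings.** A reader might infer that the schedule makes satisfaction look better than it was. The documents do not support that as fact: they give neither satisfaction by retention nor reasons for leaving, and people may leave through illness or other causes unrelated to the course. A reader might also see a contradiction between Module V and Table 1. There is none, because the end-of-training scales match the T1 column and a later questionnaire can coexist with the discussion. Nor can the plan's 15% be read as the cost of choosing T3 over T1, for the reason given in the check.

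**Conclusion.** The point holds as a low-severity weakness in design. The training-experience questionnaire is scheduled once, months after the course, so it is open to delayed recall and to selection by retention. Upward bias in satisfaction is possible but unproven, and neither its sign nor its size is fixed by the document. The range of 76.5% to 91.5% rests on an assumed 90% satisfied among responders, an assumed 15% loss through T3 and no knowledge of the lost; the 13.5-point extreme requires that none of the lost was satisfied. No hypothesis test is affected.

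The disagreement over T3 (3 months in the footnote, 6 months elsewhere) is a separate and firmer inconsistency. It also leaves the recall interval for this outcome undefined.

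**What to change.** - In the Training experience row of Table 1, mark T1 as well as T3. Keep T3 for lasting use and benefit.
- At T1, have participants complete the form themselves and return it to someone other than the trainer.
- Offer the same short form to people when they stop attending. This step, not the T1 administration, reaches early leavers.
- Report T1 and T3 results separately, with the number responding at each and the number of exit forms returned.
- State in one sentence how the Module V discussion relates to this outcome.
- Reconcile the T3 timing between the Table 1 footnote and the other sections.

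**Cost.** A few more minutes at T1, where questionnaires are already completed, and a brief contact with those who leave. Some courtesy bias remains at T1 if trainers are present.

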### Intervention Through Training

The training is structured as a blended program combining didactic and interactive educational methods, designed to strengthen health and eHealth literacy and to support diabetes self-management in older adults. The program is organized into 5 modules over a 10-week period (1 session every other week). The average duration of each session will be 90 minutes. Active engagement will be encouraged throughout the sessions, with participants involved in discussions, scenario-based activities, and guided reflection. This approach aims not only to promote meaningful learning but also to foster confidence, autonomy, and sustainable behavioral change in managing type 2 diabetes. The overarching objectives of the training program are grounded in the three key learning competencies outlined by the European Qualifications Framework, which are articulated through the following three dimensions:

Knowledge: The program aims to cultivate awareness and critical understanding regarding health and eHealth literacy. The objective is to empower participants with comprehensive knowledge of health-related issues and eHealth literacy challenges. By delving into these subjects, participants will grasp their significance and explore effective strategies for addressing them.Skills: The training is designed to equip older adults with advanced skills that are specifically tailored to their interactions with digital tools in the context of health and eHealth literacy. Through personalized instruction, participants will be equipped with the necessary capabilities to navigate digital platforms effectively, thereby fostering proficiency in the use of these tools to enhance health literacy among older adults.Competencies: The program is committed to ensuring the sustainability of the skills acquired during the training and their practical application in real-world scenarios. Beyond mere knowledge acquisition, the objective is to catalyze meaningful behavior change. The training environment is designed to encourage the adoption, adaptation, and maintenance of positive behavioral habits, thereby addressing health and eHealth literacy challenges comprehensively.

The training program is divided into the following modules:

Module I: raising awareness of eHealth and health literacy: introduction to the aims and context of JACARDI and diabetesModule II: achieving new knowledge: health literacy and self-management of diabetesModule III: achieving new knowledge: technological and nontechnological strategies to support the self-management of diabetesModule IV: practicing new skills: usability with practice sessionModule V: self-evaluation and sustainability of the improvement (final questionnaire)

Module I aims to enhance participants’ awareness of the importance of eHealth and health literacy, highlighting their crucial role in managing type 2 diabetes among older adults. To this end, the module is divided into two distinct parts: a lecture session and a group discussion. The first part focuses on analyzing the definition and relevance of eHealth and health literacy, highlighting the difficulties older adults may encounter in adopting digital tools for health care. An overview of the Italian initiatives and projects that focus on the digitization of health care services for older adults is also provided. Particular attention is paid to the obstacles to implementation, such as regulatory issues, privacy concerns, economic sustainability, and challenges posed by multimorbidity. The use of practical examples and short demonstrations facilitates the understanding of the theoretical concepts. The second part of the module consists of a group discussion, during which participants will be invited to reflect on and share their opinions on the role of technology in health care. This part of the module employs guided discussion techniques and real-world scenarios to encourage dialogue on the acceptance or rejection of technological tools and to identify the main barriers to access. The barriers include motivational limitations, deficiencies in digital skills, material constraints, and usability challenges. This configuration facilitates the learning process, combining a solid theoretical foundation and practical activities, emphasizing the direct correlation between learning objectives and final outcomes.

Module II aims to address issues related to improving self-management and health literacy among older adults with type 2 diabetes, foster a greater understanding of the disease, and support the adoption of effective strategies for the daily management of type 2 diabetes. The session is structured around interactive lessons that offer participants the opportunity to learn fundamental information about the disease and prevention of its negative consequences. During the first part, definitions and guidelines will be shared on key topics such as treatment management, importance of physical activity, adoption of a personalized nutritional plan, and diabetic foot care. The goal of this phase is to reduce inadequate health literacy, which is often associated with difficulties in understanding medical information, limited knowledge of the disease, poor adherence to treatment, worsening health, and increased costs. Classes will include hands-on demonstrations and the use of concrete examples to facilitate learning and make complex medical concepts more accessible. The second part of the session is structured as a group discussion moderated by a clinical psychologist. In this context, participants will have the opportunity to share and discuss the most common obstacles and fears encountered in the diabetes management journey as well as to discuss concerns about the consequences of the disease and the impact of the diagnosis on their lives. The methodology adopted, which is based on real-world scenarios and direct comparison, helps foster behavioral change, sustain motivation, and promote practical strategies for successfully addressing everyday challenges.

Module III is designed to assist older patients with type 2 diabetes in acquiring and understanding the concepts of health literacy and eHealth literacy. The objective is to support them to make more informed health decisions and use digital tools effectively for their physical and mental well-being. The module combines a theoretical component with a practical experience. Initially, the key concepts, the available resources, and the relevant associations and stakeholders, including peer support groups, will be presented and discussed. The goal is to demonstrate to the participants the range of technological and nontechnological strategies that are effective in enhancing eHealth skills and facilitating diabetes management. The teaching methods adopted include interactive presentations, guided discussions, and hands-on activities. The digital applications selected for the program are chosen on the basis of a preliminary study that evaluated their ease of use and reliability using focus groups and interviews. During the practical session, participants will engage in exercises designed to select safe and intuitive digital apps, with the aim of promoting a more autonomous and informed approach to managing their health. The learning-by-doing methodology will enable participants to directly test practical tools, verify their functionality, and gain greater confidence in using digital technologies, integrating these skills into their daily diabetes management. This approach facilitates the integration of digital solutions into participants’ daily routines, optimizing health management practices and fostering the development of skills useful for greater autonomy and decision-making capacity.

Module IV explores the pivotal concept of usability in the context of digital and technological devices and services, with the aim of raising awareness of interaction with technology among older patients with type 2 diabetes. The session is designed as a lecture, with the objective of conveying to participants the idea that technology is not inherently good or bad in itself. Rather, shortcomings in the usability of tools are often the main cause of frustration and, consequently, rejection. The module focuses on the most common difficulties and errors in using technology, assisting participants in distinguishing between issues stemming from insufficient digital skills and limitations related to the usability of a tool or service. The methodology combines theoretical explanations and practical activities. In the final part of the module, participants will engage in a practical usability test, with a focus on frequently used digital platforms, such as those employed for scheduling medical appointments, which are particularly relevant to the health care needs of older people. This exercise enables participants to directly experience the main usability issues encountered on these platforms, addressing the difficulties that can arise in everyday life. Through a problem-solving approach, participants will identify the most common obstacles in interacting with technology and acquire strategies to overcome them, thus improving their independence and effectiveness in using digital services. By actively participating in the hands-on exercise, patients will refine their abilities in navigating digital platforms, thereby fostering a more informed and constructive interaction with technology. This contributes not only to more independent management of digital services but also to improved health care and monitoring.

Module V is designed to encourage participants to self-reflect, with the objective of evaluating their level of awareness, knowledge, and skills in technology and digital health literacy. This session represents the final stage of the training program, including a component dedicated to evaluating the effectiveness of the educational activities and methods used during the program. The method adopted involves a trainer guiding participants through the completion of the final questionnaire, explaining its characteristics and providing practical support during the completion. During this phase, participants will complete a series of validated instruments, described in detail in the Results section of the protocol, which will measure changes in quality of life, psychological well-being, health literacy, eHealth literacy, self-efficacy, and diabetes-related distress. The use of standardized scales ensures that the assessment is measurable and comparable across multiple time points, thereby providing clear indicators of the program’s effectiveness. This quantitative evaluation is complemented by a final discussion, in which participants’ reflections, feedback, and suggestions for maintaining the skills acquired will be collected. Consequently, the evaluation process evolves from a mere descriptive exercise to one that is also actionable, as the collected data will be systematically analyzed and used to identify strengths and areas for improvement, guiding the refinement of future training cycles. The module includes instructions for completing the questionnaire, reflecting on personal progress in relation to the training objectives, and receiving constructive feedback. By actively participating in this self-assessment process, participants will have the opportunity to strengthen their digital and health literacy skills, while trainers will use the information gathered to optimize future training initiatives and ensure continuous improvement of digital health literacy interventions. In this manner, the program combines theory and practical application to foster ongoing change and hold participants accountable for their learning journey.

The training sessions will be facilitated by a multidisciplinary team of health care professionals and educators with expertise in diabetes management, health literacy, and digital health. The trainers will generally include doctors, nurses, dietitians, and clinical psychologists, each with previous experience in patient education and group facilitation. At each center, depending on the staff present and the topic of the session, the facilitators may vary.

To ensure consistency and fidelity across sessions and locations, the coordination center will be responsible for the preparation of all training materials, including manuals, slides, and practical exercises. These materials will be disseminated to all locations before the program begins. In addition, online and in-person familiarization sessions will be conducted for all trainers to review content, clarify any questions, and practice delivering the modules. This will ensure that all trainers are familiar with the course materials. Trainers will also receive guidance on specific strategies for addressing particular issues, such as managing emotional challenges or promoting autonomy, to maintain a supportive approach throughout the program. These sessions are designed to ensure that training is conducted in the same way across all centers, while still allowing trainers to adapt to the needs of participants.

